### Sample Size Calculation

A power calculation was performed to determine whether the expected number of patients is sufficient to detect an effect of cancer treatment on fertility with a reasonable power.

The calculation was performed for the primary outcome (ie, sperm count for men and AMH concentration for women) for men and women separately. Calculations were performed within each cancer entity and for each specific treatment protocol separately with a paired *t* test using Stata (release 17.0; StataCorp).

We set the effect size so that a relative risk of 50% was not missed. For the sperm count, where the mean value in healthy men is 64 million (SD 47 million) [17], this would correspond to an effect size of 0.67. For AMH concentration in women, where means and SDs can be assumed to be equal [18], it would correspond to an effect size of 0.5. The intraindividual correlation was set to 0.5 [17,18]. To account for multiple testing (analysis will be performed with 43 treatment groups for men and women separately), the Šidák correction was used, and the significance level was adjusted to 0.0006 (2-sided).

Table 1 shows that a sufficient power of >80% will be reached for most treatments. If the number of cases was twice as high and the intrapatient correlation coefficient was 0.7, a power of >80% would be reached for all treatment levels. As the study is expected to be extended, a sufficient number of patients can be expected in order to reach this goal.

**Table 1 table1:** Expected number of cases and resulting power reached per specific treatment (treatment protocols) in the most common *ICD (International Classification of Diseases)* cancer groups [19].

*ICD* cancer group	Cases, n^a^	Specific treatments (treatment protocols), n	Effect size (females/ males)^b^	Power (females/ males)^b^, %/%
Breast	2000	6	0.5/—^c^	100/—
Hodgkin lymphoma	1000	2	0.5/0.68	100/100
Bone and articular cartilage	400	3	0.5/0.68	98.6/100
Female genital organs	350	3	0.5/—	96.5/—
Male genital organs	2000	4	—/0.68	—/100
Digestive organs	200	7	0.5/0.68	14.3/41.4
Mesothelial and soft tissue	200	3	0.5/0.68	67.2/96.7
Eye, brain, and central nervous system	300	2	0.5/0.68	99.5/100
Non-Hodgkin lymphoma	300	8	0.5/0.68	26.2/64.4
Leukemia	200	5	0.5/0.68	30.6/70.8

^a^The estimation of the number of cases is based on the number of patients previously counseled and documented in the FertiPROTEKT and FERTISAVE registries.

^b^Power is calculated for each treatment protocol for men and women separately. The number of patients per protocol is calculated as the number of cases divided by the number of treatment protocols. The sex ratio is assumed to be 1:1, except for cancer of the breast and genital organs.

^c^Not available.

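### Table 1 credits every case to each sex in the seven mixed-sex cancer groups, so the printed power rests on twice the patients that the stated 1:1 sex ratio supplies

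*Protocol article*

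**What the plan says.** The Sample Size Calculation section sets out a power check for the primary outcomes, AMH in women and sperm count in men. On method it states: "Calculations were performed within each cancer entity and for each specific treatment protocol separately with a paired *t* test using Stata". For multiplicity, "the Šidák correction was used, and the significance level was adjusted to 0.0006 (2-sided"), because "analysis will be performed with 43 treatment groups for men and women separately".

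Footnote b of Table 1 gives three rules for the number of patients behind each power figure:

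- The first rule fixes the unit, which is one protocol in one sex: "Power is calculated for each treatment protocol for men and women separately".
- The second rule spreads a cancer group's patients evenly over its protocols: "The number of patients per protocol is calculated as the number of cases divided by the number of treatment protocols".
- The third rule says how a group's patients divide between the sexes: "The sex ratio is assumed to be 1:1, except for cancer of the breast and genital organs".

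Footnote a says that the case numbers come from registry counts of patients already counseled. Neither it nor the column header says that they are counts per sex.

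The text draws two conclusions. The first is: "Table 1 shows that a sufficient power of >80% will be reached for most treatments". The second concerns twice the number of cases and a within-patient correlation of 0.7, under which "a power of >80% would be reached for all treatment levels".

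**The concern.** If 400 bone tumor patients are half women and half men and are spread over three protocols, each protocol has about 66 women and 66 men. The three rules in footnote b allow no other count. The table does not appear to use it.

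This can be seen without software. Bone (400 cases of both sexes, 3 protocols) is printed with 98.6% power in women. Female genital organs (350 cases, all women, 3 protocols) is printed with 96.5%. The effect size is 0.5 in both rows. About 200 women cannot give more power than 350 women under the same test.

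This table is the article's only quantitative argument that the expected numbers suffice. The per-protocol paired comparisons that it describes are the primary analysis in the Data Analysis section. The statement about doubled numbers also supports the expectation that an extended study will reach adequate power for every treatment.

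**Working it through.** **Inputs** (all from Sample Size Calculation and Table 1)

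- Two-sided paired *t* test.
- Significance level: 43 protocols × 2 sexes = 86 tests, so α = 1 − 0.95^(1/86) = 0.000596, printed as 0.0006. The protocol counts in Table 1 do add up to 43.
- Correlation r = 0.5, so the SD of the difference is SD × √(2(1 − 0.5)) = SD.
- Effect size in women: 0.5.
- Effect size in men: half of 64 million over 47 million, 32/47 = 0.681. The table prints 0.68. The text prints 0.67, but 0.681 is the value that reproduces the table.

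**Formula.** Power is the probability that a noncentral *t* variable with n − 1 degrees of freedom and noncentrality d√n / √(2(1 − r)) exceeds the two-sided critical value at α. Fractional n is rounded down.

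**Step 1: reproduce the printed figures.** The single-sex row for female genital organs has n = 350/3 → 116 and gives 96.5%, as printed. For the mixed-sex rows, the column *Undivided* uses n = cases / protocols in each sex, and *Halved* uses n = cases / (2 × protocols).

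| Group | Cases / protocols | Printed (women/men) | Undivided: n, power | Halved: n, power |
|---|---|---|---|---|
| Hodgkin lymphoma | 1000 / 2 | 100/100 | 500, 100/100 | 250, 100/100 |
| Bone | 400 / 3 | 98.6/100 | 133, 98.6/100 | 66, 67.2/96.7 |
| Digestive organs | 200 / 7 | 14.3/41.4 | 28, 14.3/41.4 | 14, 2.6/7.8 |
| Mesothelial, soft tissue | 200 / 3 | 67.2/96.7 | 66, 67.2/96.7 | 33, 20.6/54.8 |
| Eye, brain, CNS | 300 / 2 | 99.5/100 | 150, 99.5/100 | 75, 76.5/98.7 |
| Non-Hodgkin lymphoma | 300 / 8 | 26.2/64.4 | 37, 26.2/64.4 | 18, 4.9/15.4 |
| Leukemia | 200 / 5 | 30.6/70.8 | 40, 30.6/70.8 | 20, 6.4/20.0 |

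The undivided n matches every printed value. The halved n matches only the Hodgkin row, which is at 100/100 either way and so does not discriminate. Keeping n halved and changing other settings (r of 0.7 or 0.75, α of 0.0012, a one-sided test, a normal approximation) does not reproduce the table either. Bone at half its cases gives exactly the printed mesothelial row, as it must: same protocol count, half the cases.

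**Step 2: the first conclusion.** Count protocol-by-sex comparisons. Women have 43 − 4 = 39 (no male genital protocols). Men have 43 − 6 − 3 = 34 (no breast or female genital protocols). The total is 73.

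- As printed, above 80%: women 6 + 2 + 3 + 3 + 2 = 16 (breast, Hodgkin, bone, female genital, CNS); men 2 + 3 + 4 + 3 + 2 = 14 (Hodgkin, bone, male genital, mesothelial, CNS). Total 30 of 73.
- After halving: women 6 + 2 + 3 = 11 (breast, Hodgkin, female genital); men 2 + 3 + 4 + 2 = 11 (Hodgkin, bone, male genital, CNS). Total 22 of 73.

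**Step 3: the second conclusion.** With twice the cases and r = 0.7, the SD of the difference is SD × √0.6.

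- Without the sex split, the lowest cell is digestive women: n = 400/7 → 57, power 88.1%. The sentence holds.
- With the split, n = 2 × cases / (2 × protocols). Digestive, n = 28: 35.1/76.1. Non-Hodgkin women, n = 37: 56.9. Leukemia women, n = 40: 63.4. These four cells stay below 80%.

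**Step 4: the alternative reading.** The case column adds up to 6950, of which the mixed-sex groups contribute 1000 + 400 + 200 + 200 + 300 + 300 + 200 = 2600. If those 2600 are counts per sex, the expected total is 6950 + 2600 = 9550.

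**The case against.** The strongest defence is that the mixed-sex rows already list cases per sex. The 1:1 sentence would then explain why one n serves both columns, the division by protocols would be followed literally, and both the powers and the doubled-cases statement would be correct. The fault would be one of labelling. This cannot be excluded, but nothing printed supports it. The header reads simply as cases, and footnote a describes counseled patients. The same column would also mix per-sex and total counts and understate enrolment by 2600. The table needs correction under either reading.

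Three further points have some force:

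- **Few cells change verdict.** Only bone women, CNS women and mesothelial men cross the 80% line. Counted by cancer group and sex, the cells above 80% go from 10 of 17 to 7 of 17. Digestive, non-Hodgkin and leukemia were already printed below 80%, and Hodgkin does not move.
- **The claim about most treatments is weak anyway.** By protocol and sex, only 30 of 73 exceed 80% even as printed. The halving makes this worse but is not its sole cause.
- **Consequences are bounded.** The cohort is described as exploratory, and its size comes from registry counts rather than a power target. The Data Analysis section plans false discovery rate control, which is generally less strict than the Šidák level, so the planned tests may have more power than the restated figures.

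None of this restores the printed powers, which the article presents as Šidák-level power under a 1:1 sex ratio.

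**Conclusion.** The point holds. As worded, Table 1 contradicts its own footnote: in the seven mixed-sex groups each sex is given all the cases. Six of the seven rows change when the stated ratio is applied. Three cells drop from above to below 80%: bone women 98.6 to 67.2, CNS women 99.5 to 76.5, and mesothelial men 96.7 to 54.8. In digestive, non-Hodgkin and leukemia, power falls to between 2.6% and 6.4% in women and between 7.8% and 20.0% in men. Under the same ratio, the statement that doubled cases with r = 0.7 suffice for all treatments is wrong.

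These figures assume the article's own inputs (α = 0.000596, r = 0.5, effect sizes 0.5 and 32/47) and that the case column counts both sexes together, which is the natural reading of the header and footnote a. If the counts are per sex, the powers stand, but the labelling and the implied total are wrong. This should be corrected before the power statements are relied on.

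**What to change.** Establish from the registry counts whether the mixed-sex case numbers cover both sexes or one.

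- **Both sexes together:** recompute the seven rows with n = cases / (2 × protocols), add a column with n per protocol and sex, and correct footnote b to show the division by two. Replace the sentence on most treatments with the actual count (22 of 73 protocol-by-sex comparisons above 80%). Replace the sentence on doubled cases with one naming the cells that remain below 80%.
- **Per sex:** relabel the column, delete or reword the sex-ratio sentence, and state the expected enrolment of 9550. The sentence on most treatments still needs rewording, since 30 of 73 is not a majority.

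The cost is one rerun table and two reworded sentences. No new patients or data are needed. Under the first branch the stated power becomes less favourable, and any extension should be sized from the corrected figures.

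### Table 1 power in six of the seven mixed-sex cancer groups counts patients of both sexes, although footnote b puts it per sex at 1:1, and both conclusions drawn from the table fail once n is halved

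*Protocol article*

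**What the plan says.** The section Sample Size Calculation bases power on the two primary outcomes, AMH in women and sperm count in men. The sexes are treated separately, and the calculation is run "for each specific treatment protocol separately with a paired *t* test using Stata". Footnote a says that the case numbers come from patients previously counseled and documented in two registries. Footnote b sets the number per protocol as cases divided by protocols, says that power is per protocol and per sex, and adds: "The sex ratio is assumed to be 1:1, except for cancer of the breast and genital organs".

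Two conclusions follow from the table. The first is "Table 1 shows that a sufficient power of >80% will be reached for most treatments". The second is that, with twice the cases and a within-patient correlation of 0.7, "a power of >80% would be reached for all treatment levels". The section closes by saying that an expected extension of the study should supply enough patients to reach that goal.

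**The concern.** A paired test in women with a given cancer and protocol can use only the women. Under footnote b, the n behind each mixed-sex entry should be cases / (2 × protocols). The table itself shows that this was not done. Bone has 400 cases of both sexes over 3 protocols and a printed female power of 98.6%. Female genital organs has 350 women over 3 protocols and 96.5%, with the same effect size and significance level. At a 1:1 ratio bone has about 200 women, so its female power cannot be the higher of the two.

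Table 1 is the only quantitative support for the study's size. The primary analysis tests each regimen separately, and the results go to a public platform used for counseling. A reader who trusts the printed power would give a null result in a small group more weight than it can bear.

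**Working it through.** **Inputs, all from Sample Size Calculation and Table 1**
- Effect size: women 0.5; men 0.5 × 64 / 47 = 32/47 = 0.681 (0.68 in the table, 0.67 in the text).
- Within-patient correlation ρ = 0.5.
- Two-sided significance level 0.0006 by Šidák. The text says "analysis will be performed with 43 treatment groups for men and women separately"; 43 × 2 = 86 tests give 1 − 0.95^(1/86) = 0.000596. With 43 tests it would be 0.0012.
- Cases and protocols per cancer group as printed.

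**Method.** Paired t test power from the noncentral t distribution, df = n − 1, noncentrality = d√n / √(2(1 − ρ)). With ρ = 0.5 the denominator is 1. n is rounded down.

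**Step 1: reproduce the table.** With n = cases / protocols and no division by sex, all 17 printed powers are recovered to the printed decimal, including the single-sex rows (for example female genital organs, 350/3 = 116, 96.5).

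**Step 2: apply footnote b.** Halve n in the mixed-sex rows.

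| Group | n undivided | Power, women/men (= printed) | n per sex | Power, women/men |
|---|---|---|---|---|
| Hodgkin lymphoma | 500 | 100/100 | 250 | 100/100 |
| Bone | 133 | 98.6/100 | 66 | 67.2/96.7 |
| Digestive organs | 28 | 14.3/41.4 | 14 | 2.6/7.8 |
| Mesothelial and soft tissue | 66 | 67.2/96.7 | 33 | 20.6/54.8 |
| Eye, brain, CNS | 150 | 99.5/100 | 75 | 76.5/98.7 |
| Non-Hodgkin lymphoma | 37 | 26.2/64.4 | 18 | 4.9/15.4 |
| Leukemia | 40 | 30.6/70.8 | 20 | 6.4/20.0 |

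One example needs no software. Bone per sex (400/3/2 = 66) has the same n as the undivided mesothelial row (200/3 = 66), so bone should carry the 67.2/96.7 printed for that row.

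Other settings at halved n were also tried: a one-sided level, Šidák over 43 tests, ρ = 0.7 or 0.75, and an unadjusted 0.05. None reproduces the table.

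**Step 3: the claim about most treatments.** The table has 43 protocols. Women have 43 − 4 = 39 cells and men 43 − 6 − 3 = 34, so 73 in all. After halving, the cells above 80% are:
- women: breast 6 + Hodgkin 2 + female genital organs 3 = 11;
- men: Hodgkin 2 + bone 3 + male genital organs 4 + CNS 2 = 11.

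| Count above 80% | Printed powers | n halved |
|---|---|---|
| Sex-by-protocol cells | 30/73 | 22/73 |
| Table entries | 10/17 | 7/17 |
| Protocols, in at least one sex | 23/43 | 20/43 |

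**Step 4: the claim about all treatment levels.** Double the cases and set ρ = 0.7, so the denominator is √0.6 = 0.775.
- Undivided n: the lowest power is 88.1% (digestive organs, women, n = 57). The claim is true on that n.
- n per sex: digestive organs (n = 28) 35.1/76.1; non-Hodgkin women (n = 37) 56.9; leukemia women (n = 40) 63.4. These are 7 + 8 + 5 = 20 female and 7 male cells below 80%.

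**The case against.** **The case counts may be per sex.** Footnote b does define the number per protocol as cases divided by protocols, and that is what was computed. If the mixed-sex counts were per sex, the powers would be right and the label wrong. The registry counts that would settle this are not in the article, so the possibility stays open. It is the weaker reading: neither the column label nor footnote a mentions sex, the 1:1 ratio would then play no part in the calculation, and expected cases in the seven mixed-sex groups would rise from 2,600 to 5,200. The table or its footnotes need correction on either reading.

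**Not every mixed-sex row is affected.** A reader might infer that all seven are overstated. Hodgkin lymphoma is not, and eye, brain and CNS in men drops only from 100 to 98.7.

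**The claim about most treatments on the printed figures.** A reader might say that it already fails before any correction. That holds only by sex-by-protocol cell (30/73). By table entry (10/17) or by protocol in at least one sex (23/43) the printed table shows a majority.

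**The planned analysis does not use Šidák.** One might conclude that a protocol which halves AMH would almost always be missed in the small groups. That assumes a threshold of 0.0006, but Data Analysis plans false discovery rate control, whose effective threshold depends on how many tests reject. Over an assumed range of 0.01 to 0.05, female power at halved n is 17.5 to 41.0% (digestive organs), 25.5 to 51.6% (non-Hodgkin) and 29.7 to 56.5% (leukemia). That is low, but it is not near-certain failure.

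**Low power is partly disclosed.** The table prints 14.3, 26.2 and 30.6% for women in the small groups, the study is described as exploratory, and the Discussion plans to show confidence intervals and individual variation. This softens the consequence but does not make the printed powers consistent with footnote b.

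**Conclusion.** The point holds. On the natural reading of footnote b, 12 of the 14 mixed-sex power entries in Table 1 (both sexes in six groups) rest on twice the available n. Three entries drop from above to below 80%: bone women (98.6 to 67.2), eye, brain and CNS women (99.5 to 76.5), and mesothelial and soft tissue men (96.7 to 54.8). The claim about most treatments then fails on each of the three counts, and the claim about all treatment levels fails for four table entries. The statement that an extension will reach the goal rests on the latter claim and falls with it.

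The corrected figures assume that the case counts cover both sexes and use the article's own effect sizes, correlation and significance level. Table 1 describes no deduction for loss to follow-up, which the Discussion expects, so at these case numbers the corrected powers are upper values. The small gap between 0.67 and 0.68 for the male effect size does not explain the discrepancy.

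**What to change.** 1. Recompute Table 1 with n halved in the mixed-sex groups, and print n per sex and protocol. If the case counts are in fact per sex, say so instead and correct the column label and footnote b.
2. Replace the statement about most treatments with the actual count, naming the denominator: 22 of 73 sex-by-protocol cells if n is halved.
3. Correct or delete the sentence on all treatment levels, and the statement that an extension will reach that goal.
4. Add that a non-significant result in a low-power cell is not evidence of no gonadotoxicity.

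The tests planned in Data Analysis stay as they are. Restricting low-power cells to estimates with confidence intervals would withdraw planned primary tests, and this finding does not call for that. The cost is one recalculated table and a few sentences, with no change to patients, design or endpoints. The downside is a less favourable stated power.

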### Data Analysis

The impact of cancer therapies and chemotherapies on the primary outcomes will be assessed for each *ICD* cancer group [19] and for each specific treatment regimen separately by comparing values measured before and after the gonadotoxic therapy using paired *t* tests. *P* values will be adjusted for multiple testing using the false discovery rate controlling procedure.

Consequences on other fertility parameters measured before and 12-15 months after the end of gonadotoxic therapy (ie, AMH, FSH, LH, and E2 concentrations in women and total testosterone, FSH, and LH concentrations and total sperm count, sperm concentration and motility in men) will be assessed using the same methodology, but without false discovery rate adjustment. Long-term consequences will be investigated later by comparing values measured before and 5 and 10 years after the gonadotoxic therapy. However, due to the long period until the final analysis, statistics might be adapted in relation to future development of cancer and fertility-preserving therapies.

As age was identified to potentially modify the effect of gonadotoxic therapy on female fertility, we will additionally conduct stratified analyses and document the impact of gonadotoxic therapy in the different female age groups.

Finally, the effects of different cancers, treatment protocols, age, and the presence of the patients’ children before cancer therapy on primary and secondary fertility outcomes will be analyzed using linear mixed effect models.

The frequency of patients undergoing fertility-preserving treatments, namely freezing of ovarian tissue, oocytes and embryos, testicular tissue, and sperm will be calculated for each *ICD* cancer group and for each specific treatment protocol separately and additionally presented with the associated 95% Wilson CI. Potential effects of the patients’ characteristics on the abovementioned binary outcomes will be analyzed using logistic regression analysis.

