## Methods

### Study Design

The study consists of 2 parts: first, a series of systematic reviews; second, an international multicenter prospective exploratory observational cohort study of fertility-related parameters with a long-term follow-up of the fertility of patients with cancer in university and nonuniversity public hospitals and private infertility centers in Germany, Switzerland, and Austria. All data will be uploaded on an internet-based data platform.

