### End Points

The primary end points are the AMH concentration in women and sperm count before and after gonadotoxic treatments. End points will be assessed before and 12-15 months after the end of the gonadotoxic treatments (patients with melanoma receiving adjuvant checkpoint inhibitor treatment will be evaluated every 3 months).

Secondary end points are FSH, LH, and E2 concentrations in women and total testosterone, FSH, and LH concentrations, total sperm count, and sperm motility in men. Further secondary outcome parameters are the number of patients who freeze gametes and gonadal tissue and satisfaction with the decision to have undergone fertility-preserving measures.

Long-term end points to be determined 5 and 10 years after the end of the gonadotoxic therapy are the abovementioned hormone and sperm parameters as well as the number of patients who become pregnant after gonadotoxic therapies spontaneously or after the use of frozen gametes and gonadal tissue.

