To bridge this data gap, we designed a study to analyze published data and data that will be collected in at least 3 countries by centers belonging to the FertiPROTEKT network. The data will be analyzed und disseminated via the FertiFOX web-based platform to provide patients, researchers, and clinicians access to the analysis, which will be graphically illustrated. By including patients’ representatives in the data analysis, we will ensure that the data are presented in a manner that is also understandable to patients. The data will not only be presented as a single curve presenting the means and showing odds ratios and CIs, which presents the average impact of therapies on gonadal function, but also show individual variations by presenting a set of curves.

The study has been designed to follow up on patients for at least 10 years. Such a long follow-up will enable us to evaluate how many patients have undergone fertility-preserving procedures but unfortunately did not survive. Furthermore, we will be able to estimate how many patients conceived spontaneously or by using the frozen gametes and gonadal tissue. Such an analysis is essential to evaluate the long-term efficacy of fertility preservation counseling and treatment. We are aware that some patients might be lost to follow-up. However, as the number of included patients is expected to be very high, it can be assumed that the amount of data will still be sufficiently high.

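### The paired test of percent motility covers only men with sperm at both visits: label it so, report the share without sperm, and add total motile sperm count

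*Protocol article*

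**What the plan says.** End Points in the protocol article sets the primary outcome: "The primary end points are the AMH concentration in women and sperm count before and after gonadotoxic treatments". Motility is secondary, listed with "total sperm count, and sperm motility in men". On timing, the section says: "End points will be assessed before and 12-15 months after the end of the gonadotoxic treatments".

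Data Analysis assesses the primary outcomes per cancer group and per regimen "by comparing values measured before and after the gonadotoxic therapy using paired" t tests. It then carries the method over to the secondary parameters: "total sperm count, sperm concentration and motility in men) will be assessed using the same methodology, but without false discovery rate adjustment". A later paragraph says that the effects of cancer type, protocol, age and existing children "on primary and secondary fertility outcomes will be analyzed using linear mixed effect models".

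The article does not say how motility is coded or analysed when a sample contains no sperm. On incomplete data, Anticipated Findings says only: "We are aware that some patients might be lost to follow-up", and relies on the large number of patients.

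**The concern.** A paired test needs a value at both visits. Sperm count has one in every man who gives a sample, because no sperm is a count of zero. Percent motility does not: with no sperm it is zero divided by zero. A method that suits count is therefore applied to a variable that stops existing in the men with the worst result. These men are not lost to follow-up, since they attended and gave a sample.

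At stake is how the per-regimen motility results are read. The FertiTOX platform is to show sperm quality before and after therapy, by disease, to anyone who looks, as a basis for counselling. An unlabelled motility change invites the reading that it applies to everyone given the regimen.

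**Working it through.** The article gives no SD, effect size or power for motility and no share of men without sperm after therapy, so there is no stated figure to reproduce. Every input below is an assumption unless its source is given.

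**1. Who contributes a pair.** Percent motility = motile sperm / all sperm. Total motile count = total count × proportion motile. The 64 million is the healthy mean in Sample Size Calculation; the other values are illustrative.

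| Man | Before | After | Motility change | Total motile count |
|---|---|---|---|---|
| A | 64 million, 50% | 40 million, 48% | −2 points | 32 to 19.2 million |
| B | 64 million, 50% | no sperm | undefined, no pair | 32 million to 0 |
| C | no sperm | no sperm | undefined, no pair | 0 to 0 |

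The paired test of percent motility uses man A alone and reports −2 points.

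**2. Can it separate regimens?** Let p be the share without sperm after therapy, unrelated to baseline values. Let d be the motility change in men who keep sperm, from a baseline of 50%, with their counts unchanged and unrelated to motility.

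- Paired motility result: d, whatever p is.
- Relative change in mean total motile count: (1 − p) × (50 + d)/50 − 1.

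| p | d = 0: paired test | d = 0: motile count | d = −5: paired test | d = −5: motile count |
|---|---|---|---|---|
| 10% | 0 | −10% | −5 | 0.9 × 0.9 − 1 = −19% |
| 30% | 0 | −30% | −5 | 0.7 × 0.9 − 1 = −37% |
| 50% | 0 | −50% | −5 | 0.5 × 0.9 − 1 = −55% |

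The two measures are different quantities, so this table does not show bias in percent motility; the test returns the d that was put in. It shows that percent motility cannot tell these regimens apart.

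**3. When does it understate motility loss?** Assume a baseline SD of 15 points and a before-after correlation of 0.5. The SD of change is then 15 × √(2 × (1 − 0.5)) = 15. Assume a mean change of −10 points over all men (hypothetical for those without sperm), and a correlation r between loss of motility and a normal liability to lose all sperm. The share p with the highest liability has no sperm. Among the men who remain:

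mean change = −10 + r × 15 × φ(z)/(1 − p), where z is the normal quantile of 1 − p.

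φ(z)/(1 − p) is 0.1755/0.9 = 0.195 at p = 10%, 0.3477/0.7 = 0.497 at 30%, and 0.3989/0.5 = 0.798 at 50%.

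| p | r = 0 | r = 0.5 | r = 0.8 |
|---|---|---|---|
| 10% | −10.0 | −8.5 | −7.7 |
| 30% | −10.0 | −6.3 | −4.0 |
| 50% | −10.0 | −4.0 | −0.4 |

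A simulation of 400,000 men per scenario agrees to within 0.1 point. With r = 0 nothing is understated. With r above 0 the shortfall grows with p, so it is largest for regimens that leave most men without sperm.

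**4. Do other provisions repair it?**
- The mixed models meet the same undefined values. A standard fit omits them or treats them as existing but unobserved.
- A large cohort makes a selected mean more precise and leaves the selection in place.
- Sperm count, total count and concentration do keep these men, at zero.

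**5. Group size.** Table 1 gives 200 leukemia cases and 5 protocols. With the 1:1 sex ratio in its footnote, 200/5/2 = 20 men per protocol. If half have no sperm after therapy, 10 motility pairs remain.

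**The case against.** The strongest objection is that the article never says such men are left out. Coding of follow-up samples belongs to the registry forms, and an analysis plan may hold a rule; neither is shown. If motility is scored as 0% when no sperm are found, no one drops out. This stands, and it is why the point is conditional. It does not remove the point: the article fixes a test that the raw variable cannot always satisfy, and it does not say to whom the result applies.

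Second, a reader might infer that the motility result is biased towards no harm. The documents do not support that as a general statement. Step 2 shows the test recovering the change among men with sperm, and step 3 shows understatement only if motility loss and sperm loss are related, which nothing in the article establishes. A result labelled as applying to men with sperm is a valid conditional description.

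Third, a reader might infer that the study would miss the harm. It would not: the primary count and two companion parameters are tested per regimen and hold these men at zero. Motility is one secondary end point, with no false discovery rate adjustment, in an "international multicenter prospective exploratory observational cohort study".

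Fourth, replacing percent motility by total motile count would merge a distinct quality measure into count. That also stands, so percent motility should be kept.

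**Conclusion.** The point holds in a limited form. Unless men without sperm are scored, the planned paired test of percent motility describes men with sperm at both visits. It cannot be read as a regimen's effect on all treated men, and it cannot distinguish regimens by the share left without sperm. It understates motility loss only if that loss is related to loss of sperm.

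The size cannot be fixed from the article. Over assumed shares of 10% to 50%, an assumed 10-point fall appears as anything from 10.0 points (no relation) to 0.4 points (correlation 0.8, half without sperm). The primary conclusion, the sample size calculation and Table 1 do not depend on motility. This is a cheap improvement.

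**What to change.** In End Points and Data Analysis:

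- Keep percent motility, and state that its before-after comparison applies to men with sperm at both times.
- Beside it, report for each regimen the number and share of men with no sperm after therapy.
- Add total motile sperm count (total count × proportion motile, zero when no sperm are found) as the before-after motility comparison in all men with both samples.
- Report men with no sperm at baseline separately. They go from zero to zero, can show no decline, and would otherwise pull a regimen's mean change towards none.

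Both components are already collected, so the cost is wording and one more analysis per regimen. The downside is that total motile count partly repeats total sperm count. The wording should be settled before the first results go on the platform, expected in 2026.
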